**4.3 Sample Size**

This study will be a cluster randomized trial at the level of the community health post. As a result, we need to take the intracluster correlation within individuals receiving treatment at each community health post in both the calculation of sample size and data analysis.

The two primary study hypotheses were stated earlier: one for the treatment of children with fast breathing and one for the treatment of children with fever. We will calculate a sample size for each of the study hypothesis

There are 43 community health posts in the study area. This will be a two-arm study so we will have 21 community health posts available for each arm with a 1:1 allocation. All of the calculations are made using the assumption of 80% power to show differences and a two side alpha of 0.05.

The sample size for a cluster randomized trial is based upon the intracluster coefficient (ICC). As we do not have accurate information on the expected ICC for the outcomes in this study, the sample size is presented as a series of sample size calculations given a range of the ICC values which we would expect to see.

## Treatment of children with fast breathing

We hypothesize that the proportion of children with fast breathing who receive early and appropriate treatment for pneumonia will be increased by at least 20% among CHWs trained to treat both malaria and pneumonia. Currently it is estimated that only 50% of children receive early and appropriate treatment for pneumonia. Therefore, we would be looking at increasing this to 70%.

The table below shows the total clusters, sample per clusters and total sample size for each level of ICC.

**Sample size necessary to detect a 20% increase in the proportion of children receiving early and appropriate treatment for fast breathing for various ICCs**

| Intracluster coefficient | Total Clusters | Sample per cluster | Total sample size |
| --- | --- | --- | --- |
| 0.05 | 36 | 6 | 216 |
| 0.07 | 36 | 6 | 216 |
| 0.09 | 38 | 6 | 228 |
| 0.11 | 38 | 6 | 228 |
| 0.13 | 36 | 7 | 252 |
| 0.15 | 38 | 7 | 266 |
| 0.17 | 36 | 8 | 288 |
| 0.19 | 38 | 8 | 304 |
| 0.21 | 38 | 9 | 342 |
| 0.23 | 38 | 10 | 380 |
| 0.25 | 38 | 12 | 456 |

At the largest ICC of 0.25, 38 clusters enrolling 12 subjects each, a total of 456 subjects would be necessary to show a difference between the intervention and control arms. At the smallest ICC of 0.05, the total sample size would be only 216 subjects who would be recruited from 36 clusters with 6 subjects per cluster. Therefore, within this expected range of ICC, we would need to enroll between 216 and 456 subjects. Since the ICC cannot be precisely estimated we would enroll the 456 subjects. We anticipate a drop out rate of 15%; hence we will increase our sample size to 524 children with fast breathing.

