**Treatment of children presenting with fever**

Currently 100% of children seen with fever should receive Coartem treatment. We hypothesize that with the use of an RDT, the proportion of children receiving Coartem treatment would be reduced to 80%.

**Sample size necessary to detect a 20% decrease of children not receiving Coartem for various ICCs**.

| Intracluster coefficient | Total Clusters | Sample per cluster | Total sample size |
| --- | --- | --- | --- |
| 0.05 | 38 | 2 | 76 |
| 0.07 | 40 | 2 | 80 |
| 0.09 | 42 | 2 | 84 |
| 0.11 | 34 | 3 | 102 |
| 0.13 | 36 | 3 | 108 |
| 0.15 | 36 | 4 | 144 |
| 0.17 | 36 | 5 | 180 |
| 0.19 | 38 | 6 | 228 |
| 0.21 | 38 | 12 | 456 |
| 0.23 | 40 | 33 | 1320 |
| 0.25 | 46 | 36 | 1656 |

At the largest ICC of 0.25, 46 clusters enrolling 36 subjects each for a total of 1656 subjects would be necessary to show a difference between the intervention and control arms. Since we do not have 46 clusters, and no feasible increase in subjects per arm will allow us to reduce the total clusters to 42, we would be underpowered with an ICC of 0.25. However, we would be able to meet the study enrollment needs at every other ICC. At the smallest ICC of 0.05, the total sample size would be only 76 subjects being recruited from 38 clusters with 2 subjects per cluster. Therefore, within these likely ranges of ICC we would need to enroll between 76 and 1320 subjects. Following the logic above we would enroll 1320 subjects. We anticipate a drop out rate of 15%; hence we will increase our sample size to 1518 children with fever.

All of the 49 CHWs supported by CHS will be used.

20 households per cluster will be selected through multi-stage sampling. 420 caregivers will therefore be interviewed. Since the household survey will be repeated at the end of the intervention, a total of 840 caregivers will be interviewed.

The total sample size for the study will be 2931 (524 + 1518 + 840 + 49)

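### The sample-size column labelled ICC behaves as a coefficient of variation: at a true ICC of 0.25 the pneumonia outcome has about 58–63% power, not 80%, and the fever shortfall is an artefact

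*Protocol*

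**What the plan says.** Section 4.3 bases the sample size on the intracluster coefficient and offers a table for values from 0.05 to 0.25 because the ICC is not known. It adds: "All of the calculations are made using the assumption of 80% power to show differences and a two side alpha of 0.05". There are 43 health posts, used as 21 per arm; section 4.2 matches them in pairs.

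- **Fast breathing.** "Currently it is estimated that only 50% of children receive early and appropriate treatment for pneumonia", to be raised to 70%. For the top of the range: "At the largest ICC of 0.25, 38 clusters enrolling 12 subjects each, a total of 456 subjects would be necessary to show a difference". The plan takes 456 whatever the ICC turns out to be. Then: "We anticipate a drop out rate of 15%; hence we will increase our sample size to 524 children with fast breathing".
- **Fever.** Coartem use is to fall from 100% to 80%. The table asks for 46 clusters of 36 (1656 children) at 0.25, and the text concludes that "we would be underpowered with an ICC of 0.25". It therefore settles on the 0.23 row, 40 clusters of 33 (1320), raised to 1518 for 15% drop-out.
- **Household survey.** "20 households per cluster will be selected through multi-stage sampling. 420 caregivers will therefore be interviewed". Two rounds give 840, and the study total is 2931 (524 + 1518 + 840 + 49).

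**The concern.** Two features of the tables do not fit an ICC. In the fast-breathing table, five times the ICC (0.05 to 0.25) costs only two more clusters and six more children per cluster. At ICC 0.25 and 12 children per cluster the design effect alone is 1 + 11 × 0.25 = 3.75. In the fever table the requirement explodes at the higher values, although a control proportion of 100% has no variance within or between clusters.

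This is the sizing of both primary outcomes. If the column is not an ICC, the assurance that 456 children cover the largest expected ICC fails for pneumonia. The plan then reports a shortfall for the outcome that has none and misses the one that does.

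**Working it through.** **Inputs (protocol, sections 4.2 and 4.3).** Two-sided alpha 0.05 and power 80%, so f = (1.960 + 0.842)² = 7.849. Pneumonia 0.50 vs 0.70; fever 1.00 vs 0.80. Pair-matched clusters, at most 21 per arm.

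**1. Reproducing the printed tables.** Pair-matched formula, with m children per cluster and the column entered as k:

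clusters per arm = 2 + f × [p0(1−p0)/m + p1(1−p1)/m + k²(p0² + p1²)] / (p0−p1)²

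- Pneumonia, 0.25, m = 12: 2 + 7.849 × (0.46/12 + 0.0625 × 0.74)/0.04 = 18.60 → 19 per arm → 38 (printed 38).
- Fever, 0.25, m = 36: 2 + 7.849 × (0.16/36 + 0.0625 × 1.64)/0.04 = 22.98 → 23 per arm → 46 (printed 46).

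The other 20 rows also match exactly. The unmatched form (+1 instead of +2) gives two clusters fewer in every row. Design-effect formulas that use a true ICC miss every pneumonia row; with pooled variance they ask for 40 clusters at 0.05 (printed 36) and 60 at 0.25 (printed 38).

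**2. What k means as an ICC.** ICC = k²p/(1−p). For k = 0.25: 0.0625 at p = 0.50; 0.0625 × 0.70/0.30 = 0.146 at p = 0.70.

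**3. Pneumonia power at a true ICC of 0.25, 19 per arm × 12.** Variance = (0.46/12) × 3.75/19 = 0.00757; SE = 0.0870; 0.20/0.0870 = 2.30. Power is 63.3% (normal) or 58.5% (paired t, 18 df). The same design falls below 80% above an ICC of about 0.114 (paired t) or 0.138 (normal).

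With unlimited children per cluster, the normal formula needs f × 0.46 × 0.25/0.04 = 22.6 → 23 clusters per arm (46 in all); paired t needs 25 per arm (50). Both exceed 21.

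**4. Pneumonia power for the design as it would run.** 42 clusters and 524 × 0.85 = 445 children, or 10.6 per cluster. Variance = (0.46/10.6) × (1 + 9.6 × ICC)/21.

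| True ICC | Paired t (20 df) | Normal |
| --- | --- | --- |
| 0.05 | 93% | 95% |
| 0.10 | 85% | 88% |
| 0.15 | 76% | 80% |
| 0.20 | 69% | 73% |
| 0.25 | 62% | 66% |

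**5. Fever.** The term k²p0² gives the 100% arm a between-cluster SD of 0.25, which is impossible. With k = 0.25 the formula cannot go below 2 + 7.849 × 0.0625 × 1.64/0.04 = 22.1, hence 46 clusters however many children are added. Without the control term: 2 + 7.849 × (0.16/36 + 0.0625 × 0.64)/0.04 = 10.7 → 22 clusters. At p = 0.80, k = 0.25 happens to equal an ICC of 0.25 (0.0625 × 0.80/0.20), so the excess is due to the control term alone.

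Power of 40 × 33 at a true ICC of 0.25: variance = (0.16/33) × 9/20 = 0.00218; SE = 0.0467; ratio 4.28; power 98% (paired t) to 99% (normal).

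**6. The smaller items.**

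- 456 × 1.15 = 524 and 1320 × 1.15 = 1518. After 15% loss, 445 and 1290 remain, below 456 and 1320. Dividing by 0.85 gives 537 and 1553. The printed figures tolerate 1 − 456/524 = 13.0% and 1 − 1320/1518 = 13.0%.
- 420 = 20 × 21, which is one arm. In 42 clusters, 20 households each is 840 per round.

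**The case against.** **No formula is printed, so the use of k is inferred.** That stands as a caveat. But an exact match in 22 of 22 rows, from the formula for the matched design that the protocol describes, leaves little room for another explanation. The power shortfall in step 3 does not depend on it: it takes the printed label at its word.

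**A reader might infer that 80% power is missed over the whole ICC range.** Row by row, each printed pneumonia design is below 80% if its value is a true ICC (63–78% normal, 58–73% paired t). But the plan does not run those rows; it enrols 456 whatever the ICC. Power is adequate in the lower part of the range, and the shortfall is confined to the upper part, above about 0.11 to 0.14.

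**Matching may recover some efficiency.** This is fair. The paired t calculation pays for matching in degrees of freedom and credits it with nothing, so 58% is at the cautious end. The protocol quantifies no gain, so none can be claimed.

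**The fever error oversizes.** Also true: it does not harm the power of that outcome. A reader might go further and infer that about 108 fever children (36 × 3) would do. That holds only at exactly 100% control use, and the protocol says only that all such children should receive the drug. The finding that there is no shortfall is sturdier. At an assumed 95% vs 75% and ICC 0.25, 40 × 33 gives variance (0.235/33) × 9/20 = 0.00320, a ratio of 3.53 and power of 92–94%.

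**The survey and drop-out items are minor.** Agreed. The survey is not built on the two tables. It would be too strong to say that 1680 interviews are the right number, because 10 households per cluster would equally reconcile the text with 420.

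**Conclusion.** The concern holds. The tables state an ICC but behave as a coefficient of variation. For pneumonia at a true ICC of 0.25, the stated 80% power is 58–63% for 38 × 12, or 62–66% for all 42 clusters with 445 children retained. At that ICC no number of children per cluster restores 80%. For fever, the statement that the study would be underpowered at 0.25 is wrong for a true ICC, and the 1320 and 1656 rest on a variance that cannot exist at 100%.

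These figures assume the protocol's own proportions, equal cluster sizes, a common ICC in both arms and no gain from matching. The errors run in opposite directions, so the totals are unsupported, not uniformly too small. If the column is relabelled as k, the printed pneumonia cluster counts stand at 80%, but they then cover ICCs only up to roughly 0.06 to 0.15, not 0.25.

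The drop-out inflation (short by 13 and 35 children) and the survey count are separate, minor inconsistencies.

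**What to change.** 1. Relabel the column as the between-cluster coefficient of variation k, say whether it applies within pairs, name the formula and give the implied ICC (for k = 0.25: 0.0625 at 50%, 0.146 at 70%). Alternatively, recompute both tables with a true ICC.
2. Replace the blanket 80% claim for pneumonia with power by true ICC for 42 clusters and 445 retained children, as tabulated in step 4 of the working.
3. Recompute the fever table with a control-arm variance that agrees with the assumed control proportion, preferably also for a value below 100%. Delete the statement about being underpowered. Do not adopt 108 children as a target.
4. Inflate for drop-out by 1/0.85 (537 and 1553), or state that 524 and 1518 tolerate about 13% loss.
5. Reconcile the survey: either 840 caregivers per round or 10 households per cluster. Then update the total. With the drop-out correction it becomes 537 + 1553 + 1680 + 49 = 3819 or 537 + 1553 + 840 + 49 = 2979.

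Items 1 to 3 cost protocol text and a less favourable power statement for pneumonia; no further clusters are available or asked for. Item 4 costs at most 48 more children. Item 5 costs text, or 840 more interviews if 20 households per cluster is what was meant.

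### Both enrolment targets allow for 15% drop-out by multiplying by 1.15 instead of dividing by 0.85, so each falls about 2% short of the evaluable number it is meant to protect

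*Protocol*

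**What the plan says.** Section 4.3 sizes the two primary outcomes separately. Common to both: "All of the calculations are made using the assumption of 80% power to show differences and a two side alpha of 0.05", and "we will have 21 community health posts available for each arm with a 1:1 allocation".

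- **Fast breathing.** The improvement sought is from 50% to 70%. At the largest ICC considered, 0.25, the text says that "38 clusters enrolling 12 subjects each, a total of 456 subjects would be necessary to show a difference between the intervention and control arms". It adopts that number because the ICC is uncertain, and continues: "We anticipate a drop out rate of 15%; hence we will increase our sample size to 524 children with fast breathing".
- **Fever.** The reduction sought in Coartem use is from 100% to 80%. At an ICC of 0.23 the table gives 40 clusters of 33, or 1320 children. The protocol adopts 1320 and continues: "We anticipate a drop out rate of 15%; hence we will increase our sample size to 1518 children with fever".

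Both inflated targets then enter the overall count: "The total sample size for the study will be 2931 (524 + 1518 + 840 + 49").

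No formula is given for the inflation, and drop-out is not defined as anything other than a loss from those enrolled.

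**The concern.** A drop-out allowance exists so that the required number remains after the expected loss. If a fraction d of those enrolled is lost, the target must be the required number divided by (1 − d). Multiplying by (1 + d) gives a smaller figure, because the loss applies to the enlarged group and not to the original one. The two printed targets look like the product of the second rule.

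The study's procedures fit the ordinary meaning of drop-out. Community health workers complete an identification form for each eligible child (section 5.1), data collectors look for the child at home 5 to 7 days later (section 4.14), and the caregiver's consent is sought only at that visit (section 7). Children who are not found, or whose caregivers decline, are therefore lost from those already identified. The pneumonia outcome also depends on the follow-up visit: section 3.4 requires five days of correctly dosed treatment, and adherence is recorded at that visit.

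At stake is whether the stated targets deliver the evaluable samples that the protocol itself asks for, on both primary outcomes, and whether the printed total is right.

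**Working it through.** **Inputs (all from section 4.3).** Required numbers 456 (38 clusters × 12, ICC 0.25) and 1320 (40 clusters × 33, ICC 0.23); drop-out 15%; printed targets 524 and 1518; printed total 2931.

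**1. Reproducing the printed targets.** Required number × (1 + 0.15):

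- 456 × 1.15 = 524.4, printed as 524
- 1320 × 1.15 = 1518.0, printed as 1518

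The fever figure matches exactly and the other to rounding.

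**2. Evaluable number if 15% of those enrolled are lost.** Target × 0.85, and the largest loss each target covers, 1 − required/target:

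| Outcome | Target × 0.85 | Required | Shortfall | Loss covered |
| --- | --- | --- | --- | --- |
| Fast breathing | 524 × 0.85 = 445.4 | 456 | 10.6 (2.3%) | 1 − 456/524 = 12.98% |
| Fever | 1518 × 0.85 = 1290.3 | 1320 | 29.7 (2.25%) | 1 − 1320/1518 = 13.04% |

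**3. Targets that do allow for 15%.** Required number / 0.85, rounded up:

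- 456 / 0.85 = 536.5, so 537 (13 more than 524)
- 1320 / 0.85 = 1552.9, so 1553 (35 more than 1518)

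**4. Study total.** Printed: 524 + 1518 + 840 + 49 = 2931. With only the two targets changed: 537 + 1553 + 840 + 49 = 2979, a difference of 48.

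**5. Effect on power.** The number of clusters is held at 38 and 40, and the mean cluster size falls from 12 to 445.4/38 = 11.72 and from 33 to 1290.3/40 = 32.26. The protocol does not give its sample-size formula, so two readings of its ICC were tried. In both, K is the total number of clusters and m the mean cluster size.

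- *Standard design effect.* Effective number per arm n = (K/2)·m / (1 + (m − 1)·ICC); power = Φ(|p1 − p2| / √[(p1(1 − p1) + p2(1 − p2))/n] − 1.96).
- *ICC read as a between-cluster coefficient of variation k*, which comes closer to the protocol's tables. With c = K/2 and v = [p1(1 − p1) + p2(1 − p2)]/m + k²(p1² + p2²), power = Φ(√[(c − 1)(p1 − p2)²/v] − 1.96).

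| Outcome | Reading | At required number | After 15% loss from printed target |
| --- | --- | --- | --- |
| Fast breathing | Design effect | 63.3% | 63.1% |
| Fast breathing | Coefficient of variation | 83.1% | 82.7% |
| Fever | Design effect | 99.35% | 99.34% |
| Fever | Coefficient of variation | 82.1% | 82.1% |

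The absolute levels differ between the readings because the protocol's tables do not follow a standard design effect. That is a separate matter. The change within each row is what counts here, and it is 0.4 percentage points at most.

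**The case against.** The arithmetic is hard to dispute, so the case on the other side is that it does not matter. It has four parts.

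- **Clusters drive the information, and more are available than the targets assume.** The required numbers rest on 38 and 40 clusters, whereas 42 posts are available. Under the standard design effect, 456 children over 38 clusters give an effective total of 456/3.75 = 121.6, while 445.4 over 42 give 131.0. For fever the figures are 1320/8.36 = 157.9 over 40 clusters and 164.7 for 1290.3 over 42. So the printed targets, after 15% loss, could carry more information than the design asked for. This stands if all 42 posts take part. Section 4.15 lets community leaders decline, so clusters may be lost. Even at 38 and 40 clusters the effective totals fall only to 121.0 and 157.6.
- **The required numbers are worst-case.** At the next lower ICC, the tables need 380 for fast breathing and 456 for fever, well below 445 and 1290 respectively. This is right, and it means that the shortfall bites only at the ICC on which each target is based.
- **The targets are not a cap.** Every eligible child is registered and scheduled for follow-up during a year of data collection (sections 5.1 and 10.4), and nothing stops enrolment at 524 or 1518. Accrual may exceed both. This also stands.
- **The total is unreliable in any case.** It adds children, caregivers and health workers, and a child with both fever and fast breathing could count towards both targets. Its 840 interviews come from 420 per survey round, although 20 households in each of 42 clusters would make 840 per round. The figure of 2979 therefore shows only the effect of this one correction.

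A reading that would rescue 524 and 1518 is that 15% means 15% of the required number. The protocol does not say so, and a drop-out rate does not ordinarily mean that.

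These points limit the consequence. None of them makes the printed targets agree with the printed drop-out rate.

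**Conclusion.** The error is real, occurs twice and carries into the study total. At the protocol's own 15% drop-out, the targets of 524 and 1518 leave about 445 and 1290 evaluable children against the 456 and 1320 adopted as required. They cover 13.0% loss, not 15%. The correct targets are 537 and 1553.

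The conclusion rests on reading drop-out as a proportion of those enrolled and on taking 456 and 1320 as given. It does not depend on how those two numbers were derived. The consequence is small: about 2% fewer evaluable children than required and at most about 0.4 percentage points of power with the planned cluster numbers. This is a correction to make, of low priority, and not a weakness in either primary comparison.

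**What to change.** In section 4.3, do one of the following:

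- restate the targets as 537 children with fast breathing and 1553 with fever, and give the calculation (required number divided by 0.85); or
- keep 524 and 1518 and state that they allow for 13% drop-out.

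If the first option is taken, update the study total. With the other components as printed it becomes 2979, but the survey component should be checked before a new total is issued. If 456 or 1320 is revised for any other reason, apply the divisor 0.85 to the revised number.

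The second option costs a change of wording. The first adds 48 children to the stated targets, in a study that already registers every eligible child for a year, so it should need no new procedure.

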**Treatment of children presenting with fever**

Currently 100% of children seen with fever should receive Coartem treatment. We hypothesize that with the use of an RDT, the proportion of children receiving Coartem treatment would be reduced to 80%.

**Sample size necessary to detect a 20% decrease of children not receiving Coartem for various ICCs**.

| Intracluster coefficient | Total Clusters | Sample per cluster | Total sample size |
| --- | --- | --- | --- |
| 0.05 | 38 | 2 | 76 |
| 0.07 | 40 | 2 | 80 |
| 0.09 | 42 | 2 | 84 |
| 0.11 | 34 | 3 | 102 |
| 0.13 | 36 | 3 | 108 |
| 0.15 | 36 | 4 | 144 |
| 0.17 | 36 | 5 | 180 |
| 0.19 | 38 | 6 | 228 |
| 0.21 | 38 | 12 | 456 |
| 0.23 | 40 | 33 | 1320 |
| 0.25 | 46 | 36 | 1656 |

At the largest ICC of 0.25, 46 clusters enrolling 36 subjects each for a total of 1656 subjects would be necessary to show a difference between the intervention and control arms. Since we do not have 46 clusters, and no feasible increase in subjects per arm will allow us to reduce the total clusters to 42, we would be underpowered with an ICC of 0.25. However, we would be able to meet the study enrollment needs at every other ICC. At the smallest ICC of 0.05, the total sample size would be only 76 subjects being recruited from 38 clusters with 2 subjects per cluster. Therefore, within these likely ranges of ICC we would need to enroll between 76 and 1320 subjects. Following the logic above we would enroll 1320 subjects. We anticipate a drop out rate of 15%; hence we will increase our sample size to 1518 children with fever.

All of the 49 CHWs supported by CHS will be used.

20 households per cluster will be selected through multi-stage sampling. 420 caregivers will therefore be interviewed. Since the household survey will be repeated at the end of the intervention, a total of 840 caregivers will be interviewed.

The total sample size for the study will be 2931 (524 + 1518 + 840 + 49)

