Household surveys will be conducted at the beginning (baseline), and at the end of the project to allow us measure some of the outcomes. These surveys will collect information on demography, care seeking behaviors, recent morbidity and mortality, preventive health measures especially for malaria, knowledge of danger signs, adherence to treatment, utilization and acceptability of CHW services, opinion about CHWs. Women resident in the study area aged 15 to 45 years who have at least one child under 5 years will be enrolled for this survey. One member per household will participate. Where there is more than one eligible member, the oldest will be selected. The data collectors will conduct the household surveys. This work will be independent of the follow-up visits. Eligible women will be enrolled based on the inclusion and exclusion criteria irrespective of whether they received care from a CHW or not. Women will be asked about the recent illnesses of their children, including about disease-specific symptoms, whether they sought care, what kind of care they sought, and what kind of treatment they received/followed. The post intervention household survey will also collect information on the acceptability of the intervention.

The CHWs and some opinion leaders in the communities will also be interviewed on their views on the intervention.

- 1. **Supervision of Data Collectors**

Supervision of data collectors will be achieved by assigning 6 DCs to a DS. The DS will visit and work with each of the assigned DC at least once every two weeks. The DS will watch the DC performing part of the assigned job followed by a discussion based on the observations and the DC’s general performance. Any DC whose performance consistently falls below average will be fired and replaced by one of the people on “shelf”.

The supervisors will make three types of supervisory visits

i. Scheduled visits

The Supervisor will visit a home at the same time as a DC, having made an appointment with DC

ii. Random unscheduled visits

The Supervisor will visit a DC unannounced and not by appointment. This visit will provide an opportunity for the supervisor to pick up any “bad” practices that may have cropped up in the course of the field work.

iii. Check visits

The Supervisor will visit a home on his own without the presence of the DC. This visit is performed for several reasons including:

- - - Obtain information from the home whether a reported visit by the DC was made

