## 10.4 Study Timeline

The study will take two years to complete, six months for preliminary activities, which will include baseline data collection and formative research, one year of intervention and data collection, and six months of data analysis, reporting and dissemination.

A proposed timetable for ZIMMAPS is presented below.

| Table 1: TIMELINEACTIVITIES | ***Year and Months***  ***2007 2008 2009*** | | | | | | | |
| --- | --- | --- | --- | --- | --- | --- | --- | --- |
| 6-8 | 9-11 | 12-2 | 3-5 | 6-8 | 9-11 | **12-2** | **3-5** |
| IRB Approvals | **X** | **X** |  |  |  |  |  |  |
| Community sensitization activities | **X** | **X** |  |  |  |  |  |  |
| Training of CHW |  | **X** |  |  |  |  |  |  |
| Pilot testing of study instruments |  | **X** |  |  |  |  |  |  |
| Finalization of study instruments |  | **X** |  |  |  |  |  |  |
| Implementation of integrated Management and data Collection |  |  | **X** | **X** | **X** | **X** |  |  |
| Interim analysis/DSMB review |  |  |  |  | **X** |  |  |  |
| Preliminary data analyses/abstracts |  |  |  |  |  |  | **X** |  |
| Data analysis workshop (in Zambia) |  |  |  |  |  |  |  | **X** |
| Manuscripts/reports written |  |  |  |  |  |  |  | **X** |

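### The household survey total of 420 caregivers per round counts 21 clusters, although the trial has 42, and the error carries into the 840 and the study total of 2931

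*Protocol*

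**What the plan says.** Section 4.2 defines a study cluster as the catchment area of a community health post and matches the clusters in pairs before randomisation. Section 4.3 counts 43 posts in the area and states that "we will have 21 community health posts available for each arm with a 1:1 allocation". Under the fever hypothesis, the same section treats 42 as the number of clusters that the trial can use.

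The survey is sized at the end of that fever subsection: "20 households per cluster will be selected through multi-stage sampling. 420 caregivers will therefore be interviewed". The next sentence doubles the figure: "Since the household survey will be repeated at the end of the intervention, a total of 840 caregivers will be interviewed". The section closes with a study total of 2931, the sum of 524 children with fast breathing, 1518 with fever, 840 survey respondents and 49 community health workers (CHWs).

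Section 5.1 describes the survey itself. It enrols women aged 15 to 45 living in the study area who have a child under 5, whether or not they used a CHW. It sets no limit by arm. On timing it says: "Household surveys will be conducted at the beginning (baseline), and at the end of the project to allow us measure some of the outcomes". Later in the same section the second round is called post-intervention. Section 10.4 places the first round in the preparatory half-year: "six months for preliminary activities, which will include baseline data collection and formative research". One year of intervention follows, then six months of analysis and reporting.

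**The concern.** The protocol presents 420 as following from 20 households per cluster, and with 42 clusters it does not. A field team with both instructions has three ways to proceed: interview 20 in every cluster and double the planned number, stop at 420 and visit half the clusters, or drop to 10 per cluster without saying so. These are different surveys with different workloads and precision, and the protocol does not choose between them.

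The survey is there to measure some of the outcomes and to collect acceptability data. Its questions on care seeking make it a plausible source for the section 3.6 outcome on seeking care within 24/48 hours of onset, although section 3.6 names no source. Which clusters are visited decides whether the arms can be compared and how precisely.

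The workload also differs. The survey is done by the data collectors, of whom section 4.9 provides 12. One round is 420 / 12 = 35 interviews each under the stated total, and 840 / 12 = 70 under the per-cluster rule.

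**Working it through.** **Inputs.** Households per cluster: 20 (4.3). Clusters: 21 per arm, two arms, so 42 (4.3). Rounds: 2 (4.3). Other components of the total: 524, 1518 and 49 (4.3).

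**Reproducing the stated figures.**
- Per round: 20 x 21 = 420, an exact match.
- Two rounds: 2 x 420 = 840.
- Study total: 524 + 1518 + 840 + 49 = 2931.

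The additions are right, so the error enters only at the 420.

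**Could another cluster count explain 420?**
- All 43 posts: 20 x 43 = 860.
- The 40 clusters of the fever design chosen in 4.3: 20 x 40 = 800.
- The 38 clusters of the fast-breathing design: 20 x 38 = 760.
- Section 4.9 has 12 data collectors at 2 per cluster, which implies 6 clusters in a looser sense of the word: 20 x 6 = 120.

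None gives 420. Only 21 does.

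**Applying the rule to the trial's clusters.**

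| Quantity | Stated | 20 in each of 42 | 10 in each of 42 |
| --- | --- | --- | --- |
| Per round | 420 | 840 | 420 |
| Two rounds | 840 | 1680 | 840 |
| Study total | 2931 | 524 + 1518 + 1680 + 49 = 3771 | 2931 |

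The gap is 840 interviews over the study.

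**Precision, as an illustration only.** The protocol gives no ICC, power or precision target for the survey. I borrow the ICC range 0.05 to 0.25 that 4.3 uses for the treatment outcomes and assume a proportion near 50% and a comparison between arms at one round. With m interviews per cluster, the design effect is 1 + (m - 1) x ICC:
- m = 10: 1.45 to 3.25.
- m = 20: 1.95 to 5.75.

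The 95% half-width is 1.96 x sqrt(0.25 x design effect x (1/n1 + 1/n2)), where n1 and n2 are the interviews per arm.

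| Design | n1, n2 | Half-width, ICC 0.05 | Half-width, ICC 0.25 |
| --- | --- | --- | --- |
| 20 in each of 42 | 420, 420 | 9.4 points | 16.2 points |
| 10 in each of 42 | 210, 210 | 11.5 points | 17.2 points |
| 20 in each of 21, split 10 and 11 clusters | 200, 220 | 13.4 points | 23.0 points |

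For the same 420 interviews, spreading them over all 42 clusters is more precise than concentrating them in 21.

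**Timing.** In the section 10.4 timetable the intervention quarters run from December 2007 to November 2008, and the analysis and writing quarters run to May 2009. The end of the intervention and the end of the project are therefore about six months apart.

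**The case against.** The best defence is the phrase multi-stage sampling. A first stage could select 21 of the 42 clusters and a second stage 20 households in each, which would make 420 correct. The reading is possible, but the protocol does not state such a stage, a number of clusters to select or a rule by arm. It would also be an awkward design: 21 is odd, so it can neither divide evenly between two arms nor consist of whole matched pairs.

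It is also fair to say that the documents do not show whether the 20 or the 420 is the slip, and that the survey feeds neither primary outcome in section 3.4. Both points stand. They limit the weight of the finding and are the reason for offering two corrections.

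A reader might infer more than the text supports:
- **That the control arm is left out**, because 420 equals one arm's clusters. Section 5.1 recruits across the study area without restriction by arm, and 10 households in each of 42 clusters also gives 420 with both arms present.
- **That the two rounds fail a same-season comparison.** The protocol states no such aim, and in a concurrent comparison season would act on both arms. The post-intervention label and the analysis-only final quarters favour a second round at about November 2008, which can match a baseline in June to November 2007.
- **That the survey is the only source on children who bypass CHWs.** Section 5.1 also collects facility records, which cover those who reach a facility.

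**Conclusion.** The survey size is wrong as written, or at best cannot be reconciled with the stated design. The rule of 20 per cluster and the total of 420 agree only for 21 clusters, half the trial's 42. Following the rule gives 840 per round in place of 420, 1680 in place of 840, and a study total of 3771 in place of 2931. This rests only on the protocol's own definition and count of clusters. The half-widths rest on an assumed ICC and proportion and are not needed for the conclusion.

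The consequence is moderate. A declared sample size is off by a factor of two and the clusters to be visited are unspecified, but the power statements for the two primary hypotheses are untouched. A controlled comparison remains possible with 420 interviews if they are spread over both arms. The two datings of the second round are a minor conflict of wording.

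**What to change.** In section 4.3, state that all 42 clusters in both arms are surveyed in each round, and adopt one consistent set of figures:
- **10 households in each of 42 clusters:** 420 per round, 840 in two rounds, and the total of 2931 unchanged. The cost is somewhat more travel, since every cluster is visited for fewer interviews.
- **20 households in each of 42 clusters:** restate 840 per round, 1680 in two rounds and 3771 in total. The cost is 840 further interviews over the study.

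The first option keeps every stated total. Under the illustrative assumptions it gives up 1 to 2 points of half-width against the second (11.5 against 9.4 at ICC 0.05, 17.2 against 16.2 at ICC 0.25). If a first stage that selects clusters was intended, section 4.3 should instead give the number selected and the allocation by arm and matched pair.

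In section 5.1, change the timing of the second round to the end of the intervention, to match section 4.3. This is a change of wording only.
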